## Abstract

Supplemental Digital Content is available in the text

## Introduction

1

The literature describes muscle fatigue as muscle inability to maintain the strength and potency of its contractility, resulting in decreased strength, impaired motor control, and, consequently, leading to pain.^[1,2]^

Early muscular fatigue negatively influences the performance of targeted exercises, whether these exercises are performed by people with fibromyalgia, chronic obstructive pulmonary diseases, chronic fatigue, healthy elderly, athletes, and individuals presenting spasticity.^[3–8]^

Several biochemical events are related to the process of peripheral fatigue, resulting in alterations that may impair the mechanism of muscular contraction. These alterations may be triggered by modifications of creatine phosphate, glycogen, and lactic acid.^[1]^

Lactic acid diluted in body fluids is named “lactate,” and lactic acid is known as a by product of anerobic glycolysis observed in high-intensity and short-duration exercises. When not eliminated, the lactic acid dissociates and thus is converted into lactate, which causes the accumulation of H+ ions leading to muscular acidosis. With the acid concentration in the muscle there are alterations in the permeability of the sarcoplasmic reticulum, promoting the displacement of the calcium of the intramuscular environment, which directly interferes in the coupling of the crossed bridges of actin and myosin, compromising the contraction force. Moreover, the influence of the H+ ions promotes the state of exhaustion, interrupting the breakdown of glycogen and influencing the levels of ATP.^[1,9]^

Currently, changes in the epidemiological profile of global pathologies are occurring, because it is decreasing the rates of communicable diseases and increasing the rate of noncommunicable diseases, and 1 of the main factors of this inversion is stroke. A study carried out by the Global Burden of Disease, Injuries, and Risk Factors demonstrated that vascular diseases are the leading causes of death in the world and strokes are in second place. In addition, strokes are the leading cause of morbidity in the world population. In the United States, of the 795,000 new cases, 26% present difficulties in daily activities and 50% have reduced mobility.^[10]^

One of the consequences of a stroke is spasticity, characterized by the increase in muscle tone, which is velocity-dependent and is due to the hyperexcitability of the stretch reflex. Spasticity is responsible for triggering changes in sensory, proprioceptive, and musculoskeletal systems, for example, the reduction of blood circulation between muscle fibers.^[11–14]^

Phototherapy is an innovative and noninvasive alternative in the treatment and/or prevention of exercise-induced muscle fatigue, tissue injury, and in analyzing the processes involving mitochondrial function.^[2,15]^ In the literature, several studies have shown that the use of low-level laser therapy (LLLT) has positive effects on muscle fatigue attenuation and postexercise muscle recovery, when therapy is applied to before exercising.^[15–19]^

Considering the reports of studies on the benefits of using LLLT in the intact musculoskeletal system, it is believed that it may be of great value to use this resource in the treatment of the spastic muscle. dos Reis et al^[20]^ initiated a study that innovated the field of research with LLLT, applying it to the spastic musculature of knee extensors, observing a positive effect on the reduction of blood lactate, increased time preceding fatigue, and greater generation of muscular torque.

After this summary, it is believed that more studies, aimed at better understanding the effects of LLLT on the intact and spastic musculature, will be of great value in the area of motor sensory rehabilitation.

Therefore, the aim of this study is to evaluate the effects of LLLT in relation to muscular fatigue of the biceps brachii muscle of healthy individuals and spastic individuals.

## Methods

2

### Ethics

2.1

The project was approved by the Ethics and Research Committee of the Universidade do Vale do Paraíba (CAAE 94812618.8.0000.5503) on October 3, 2018, and subsequently registered in ClinicalTrials.gov (NCT03753984). All participants agreed and signed the free and informed consent term.

### Study design

2.2

This is a cross-sectional, comparative, randomized, placebo, and double-blind clinical trial. Thirty healthy individuals and 30 individuals with after effects of spastic hemiparesis of both sexes will be recruited, totaling 60 individuals. The study will be divided into 2 phases, with phase I being performed with healthy individuals and phase II performed with individuals with spastic hemiparesis. The study will be carried out at the Laboratório de Engenharia e Reabilitação Sensório Motora, belonging to the Instituto de Pesquisa & Desenvolvimento of Universidade do Vale do Paraíba (Brazil).

### Groups

2.3

All study participants will go through all groups, that is, both healthy individuals (phase I) and individuals with spastic hemiparesis (phase II) will pass through the 3 groups.

The clinical trial will be performed in 3 moments, which will be described below:

1.Control group: Individuals will not undergo LLLT, and will perform the muscular fatigue induction protocol.2.LLLT group: Individuals will be submitted to LLLT and subsequently will perform the muscular fatigue induction protocol.3.Placebo group: Individuals will be submitted to LLLT; however, with the device turned off and subsequently will perform muscular fatigue induction protocol.

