### Randomization and blinding

2.5

All individuals (phase I and phase II) will go through all the study groups (control group, placebo group, and LLLT group) with a minimum interval of 7 days between them; however, all individuals will initiate the protocol in the control group.

The randomization of the sample will be performed in the second session in which the individuals will be divided into two classes: class A and class B. Individuals who draw class A will start in the placebo group and finalize in the LLLT group, whereas individuals who draw class B will start in the LLLT group and subsequently perform the placebo group, making it a cross study.

Researcher 1 will be responsible for the instrumentation of the LLLT apparatus, whereas researcher 2 will be responsible for analyzing the data. Only researcher 1 will know in which group the individual will be allocated, and the type of treatment used will be hidden from researcher 2 and the participant. Figure 1 shows the flowchart indicating the randomization of the sample.

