### Low-level laser therapy

2.7

The protocol for the application of LLLT will be performed through the continuous punctual transcutaneous direct method to radiate 16 points in the biceps brachii muscle with approximately 1 cm of distance between the points.

This will be done using a laser diode, with infrared λ = 808 nm, 0.028 cm^2^ of beam area, 100 mW power, a power density of 3.5 W/cm^2^, 4 Joules/point of energy, and an energy density of 142.8 J/cm^2^.

During the LLLT application all biosafety measures will be adopted, that is, all those present at the collection site will be properly equipped with safety goggles suitable to the wavelength used and the light pointer will be covered with a plastic protective film.

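### The placebo is a switched-off laser in a crossover where every participant meets both device states, so the claimed participant blinding is at risk, though not shown to fail

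*Protocol article*

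**What the plan says.** Section 2.2 (Study design) states: "This is a cross-sectional, comparative, randomized, placebo, and double-blind clinical trial". Section 2.5 (Randomization and blinding) says that "the type of treatment used will be hidden from researcher 2 and the participant". Only researcher 1, who handles the laser, knows the allocation.

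Section 2.3 (Groups) gives the placebo rule: "Individuals will be submitted to LLLT; however, with the device turned off and subsequently will perform muscular fatigue induction protocol".

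Section 2.5 also sets the crossover. Participants "will go through all the study groups (control group, placebo group, and LLLT group) with a minimum interval of 7 days between them". The control session always comes first, and the order of the other two is drawn: "Individuals who draw class A will start in the placebo group and finalize in the LLLT group". Class B takes the reverse order.

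Section 2.7 (Low-level laser therapy) describes an infrared diode at 808 nm applied at 16 points, with "100 mW power, a power density of 3.5 W/cm^2^, 4 Joules/point of energy, and an energy density of 142.8 J/cm^2". Everyone present wears goggles and the tip is covered with a plastic film; both are presented as safety measures. Section 2.9 (Study protocol) gives placebo and LLLT sessions one common order of events, including the application step and a 3-minute wait afterwards.

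**The concern.** The article claims that participants are blinded, and the only device-level means it names is leaving the device unpowered. In a parallel trial a participant would meet one device state and have nothing to compare it with. Here each participant meets the running device in one session and the dead device in another, and section 2.4.1 requires preserved cognition. If the powered device gives any sign of operating, such as a display, a sound or an indicator light, its absence in the other session could reveal which was which.

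Two outcomes respond readily to what the participant believes. Pain on the visual analog scale is self-reported (section 2.6.4), and torque comes from maximal voluntary contractions (section 2.6.3), which depend on effort. If participants could tell the sessions apart, LLLT versus placebo would mix any laser effect with an effect of expectation. Because control is always first, this is the only randomised contrast, so no other randomised comparison could separate the two.

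**Working it through.** The point rests on the text. The only arithmetic concerns how long a matched sham would have to run.

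**Passages side by side**

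1. Claim: double-blind (2.2), with treatment hidden from the participant (2.5).
2. Means: the device is off in the placebo session (2.3).
3. Exposure: each participant has both an LLLT and a placebo session, at least 7 days apart, in either order (2.5).
4. What limits cues: the beam is infrared, goggles are worn and the tip is covered (2.7); both conditions follow the same sequence (2.9).
5. What these do not reach: items in step 4 act on the beam and on the order of events. None acts on whether the device is seen or heard to be working.
6. What is not stated: whether the device gives any light, sound or warmth, and whether the participant can see it.

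Steps 1 to 5 show that the stated sham leaves a possible route to unblinding. Step 6 is why they do not show that the route is open.

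**Length of the application**

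Inputs, all from section 2.7: power 100 mW = 0.1 W; beam area 0.028 cm²; energy 4 J per point; 16 points.

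The article's own figures are reproduced first:

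- Power density = power / area = 0.1 / 0.028 = 3.57 W/cm² (stated 3.5).
- Energy density = energy / area = 4 / 0.028 = 142.86 J/cm² (stated 142.8).

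Both agree apart from rounding or truncation, so the inputs are consistent. Then:

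- Time per point = energy / power = 4 / 0.1 = 40 s.
- Total active emission = 16 × 40 s = 640 s = 10 min 40 s.

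The article gives no time per point for either condition. The 40 s is implied by the active settings. With no emission, energy and power fix no time for the placebo, so a matched duration needs to be written down.

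**The case against.** The strongest reply is that the fact on which everything turns is not in the article. The mechanism needs a cue that participants can notice, and none is described. Section 2.5 says plainly that treatment is hidden from the participant, and the beam is infrared and viewed, if at all, through goggles. This stands in part: it rules out saying that blinding fails. It does not remove the point, because switching the device off is a stated rule rather than an omitted detail, and a better rule is available at little cost.

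A reader might also infer more than the text supports in four ways:

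- **That placebo is shorter, and so changes the rest before the contractions.** No section says so. The natural reading of section 2.3 is the same application without emission, section 2.9 gives both conditions one sequence, and an operator can time with any clock. A shorter placebo is conjecture.
- **That the lack of a blinding check is a defect.** A condensed article may leave this to the full protocol. It is at most an optional addition.
- **That a false-positive rate can be attached.** Any such rate would depend wholly on an assumed expectation effect, for which the article gives no figure.
- **That all outcomes are equally exposed.** Electromyography, thermography and blood lactate are instrument readings and less directly open to expectation, although effort can still influence them.

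**Conclusion.** The point holds as a weakness in how the sham is defined. Participant blinding is asserted, but the means named for it does not mask any operating cue the device may give, and the crossover lets every participant compare the two states. Blinding is therefore at risk; the article does not show that it is lost.

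The size cannot be stated. It depends on whether the powered device gives noticeable cues and on how far expectation moves pain scores and maximal effort, and the article is silent on both. If the device gives no perceptible sign of operating, the consequence may be nil. If it does, the affected comparison is the trial's only randomised one. This supports a cheap improvement to the stated method, not a conclusion that the results would be invalid.

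**What to change.** In section 2.3, replace the switched-off rule with an operated sham. The device is powered and handled exactly as in the active session, with emission disabled or the tip opaquely covered under the film already in use. It is held at the same 16 points for the same time per point as active; on the stated settings that is 40 s per point and 640 s in total. If this is already the practice, one sentence saying so resolves the point.

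Optionally, ask participants after sessions 2 and 3 which condition they think they received. The question should go to participants only, since researcher 1 knows the allocation.

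The cost is a change of wording, a cap or an emission-disabled setting, and minor set-up work. Only if placebo would have been shorter does it add session time, at most 640 s (about 11 minutes) per participant.

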### Volunteers

2.4

Healthy and poststroke volunteers (with spastic hemiparesis) will be contacted.

#### Inclusion criteria

2.4.1

Below are described the inclusion criteria for phase I (healthy individuals) and for phase II (poststroke individuals):1.Inclusion criteria for healthy volunteers (phase I):Age between 20 and 80 yearsBoth sexesPreserved cognition and preservation of the ability to respond to verbal stimuliDisplay the “insufficient active” or “active” indexes on the scale of the International Physical Activity Questionnaires (IPAQ)2.Inclusion criteria for poststroke volunteers (phase II):Individuals with medical diagnosis of strokeBoth sexesIndividuals with physiotherapeutic diagnosis of spastic hemiparesis with brachii predominancePreserved cognition and preservation of the ability to respond to verbal stimuliTime of injury: after 12 monthsPatients with a maximum of second degree spasticity according to the modified Ashworth scale and minimum muscle strength of 1 in the biceps brachii muscle.

#### Exclusion criteria

2.4.2

Below is described the exclusion criteria for phase I (healthy individuals) and for phase II (poststroke individuals):1.Exclusion criteria for healthy volunteers (phase I):Having musculoskeletal impairment of the dominant upper limbPracticing physical activity with weights (body building)Presence of active infection and eruptions in the dominant upper limbLimiting pain that precludes the performance of the evaluation protocolIngestion of analgesic and/or anti-inflammatory drugs and/or medicines containing corticosteroids or steroidsClassification of Fitzpatrick: phototypes V and VIPresence of malignant neoplastic lesionPresence of active infection and eruption at the site of electrode applicationHypoesthesia and/or hyperesthesia and/or anesthesia of the limb to be applied to LLLT2.Exclusion criteria for poststroke volunteers (phase II):Presence of active infection and eruptions in the dominant upper limbLimiting pain that precludes the realization of the evaluation protocolIngestion of analgesic and/or anti-inflammatory drugs and/or medicines containing corticosteroids or steroidsClassification of Fitzpatrick: phototypes V and VIPresence of malignant neoplastic lesionPresence of active infection and eruption at the site of electrode applicationHypoesthesia and/or hyperesthesia and/or anesthesia of the limb to be treatedMuscular contractures and articular deformitiesUncontrolled arterial hypertensionIndividuals who present other neurological and/or orthopedic alterations associatedWernick or Broca aphasia

### Randomization and blinding

2.5

All individuals (phase I and phase II) will go through all the study groups (control group, placebo group, and LLLT group) with a minimum interval of 7 days between them; however, all individuals will initiate the protocol in the control group.

The randomization of the sample will be performed in the second session in which the individuals will be divided into two classes: class A and class B. Individuals who draw class A will start in the placebo group and finalize in the LLLT group, whereas individuals who draw class B will start in the LLLT group and subsequently perform the placebo group, making it a cross study.

Researcher 1 will be responsible for the instrumentation of the LLLT apparatus, whereas researcher 2 will be responsible for analyzing the data. Only researcher 1 will know in which group the individual will be allocated, and the type of treatment used will be hidden from researcher 2 and the participant. Figure 1 shows the flowchart indicating the randomization of the sample.

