### Study protocol

2.9

Initially, an assessment of the individual will be carried out to analyze whether it fits into the study in question, considering the inclusion and exclusion factors already described. The individuals of the poststroke group will undergo the subjective spasticity assessment by three physiotherapists (double blind), through the modified Ashworth scale and manual evaluation of muscle strength. The term of free and clarified consent will be presented (Appendix A).

All volunteers will start in the control group and then on the second contact they undergo the study randomization as described above. The experiment procedures will be standardized in the 3 study groups according to the following sequence of events: placement of the surface electrodes in the biceps brachii muscle, climatization of the individual for 10 minutes during which the VAS and initial blood lactate measurement (baseline measurement) will be made, and after 10 minutes of air conditioning image 1 will be captured by means of infrared thermography.

To perform the muscular fatigue induction protocol of the biceps brachii muscle, the individual will be positioned at the Scott bench with the elbow at 45°. An inelastic band will have 1 of its fixed extremities in the traction dynamometer and the other end positioned on the forearm of the volunteer to perform the MIVC protocol of the brachii biceps muscle.

The protocol consists of 3 MIVCs during 50 uninterrupted seconds with an interval of 50 seconds between each contraction. During the contractions the myoelectric activity and muscular strength will be collected synchronically.

The assessments after the MIVC will be performed at three distinct moments (3, 15, and 25 minutes) following the same sequence of events: capture of the image by means of infrared thermography (images 3, 4, and 5) and blood lactate measurement.

The placebo group and the LLLT group will first undergo the climatization for 10 minutes, VAS application, blood lactate measurement (baseline measurement), image 1 capture by means of infrared thermography and LLLT application. After 3 minutes, the capture of image 2 will be performed by infrared thermography, and the surface electrodes will be positioned in the biceps brachii muscle. Subsequent events were the same as above.

For a better visualization of the sequence of events of the study a flowchart was made as shown in Fig. 2.

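### Control is session 1 for every participant, so comparisons with control are confounded with any first-session effect; only LLLT versus placebo is randomised, yet the plan does not except control from its comparisons

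*Protocol article*

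**What the plan says.** Section 2.5 (Randomization and blinding) sends every participant, healthy or post-stroke, through three conditions "with a minimum interval of 7 days between them", and adds: "however, all individuals will initiate the protocol in the control group". Section 2.9 (Study protocol) repeats this: "All volunteers will start in the control group and then on the second contact they undergo the study randomization".

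The draw comes after control is finished: "The randomization of the sample will be performed in the second session in which the individuals will be divided into two classes". It yields two orders. For class A, "Individuals who draw class A will start in the placebo group and finalize in the LLLT group". For class B, "individuals who draw class B will start in the LLLT group and subsequently perform the placebo group". The only sequences are therefore control–placebo–LLLT and control–LLLT–placebo.

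Section 2.3 (Groups) counts control as one of three groups and describes it as the fatigue task with no laser application. Section 2.8 (Outcomes) obtains the outcomes by comparing data between the groups. Section 2.10 (Statistical analysis) plans comparisons within and between groups to assess LLLT. Neither 2.8 nor 2.10 excepts control. Section 2.2 (Study design) describes the whole study in one phrase: "This is a cross-sectional, comparative, randomized, placebo, and double-blind clinical trial".

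**The concern.** Each visit repeats the same demanding task: three 50-second maximal isometric contractions on a Scott bench against a dynamometer. Performance on such a task can change between a first and a later attempt through learning, familiarity or adaptation to the earlier bout. No familiarisation visit is described. The interval of at least 7 days addresses carry-over of the laser or of fatigue, not learning.

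Because control always comes first, a change of this kind is part of every difference between control and a later condition. More participants would not remove it. Control is also open to the participant, since no device is applied, so expectation may differ as well.

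At stake is what the trial may conclude. As written, a significant LLLT–control difference could be reported as the result of a randomised, double-blind comparison, which it is not.

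**Working it through.** The article gives no power, SD or effect-size figure, so there is no planned number to reproduce.

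**Inputs from the article.** 30 people per phase, 60 in total (2.2); sequences C–P–L and C–L–P (2.5); significance level 0.05 (2.10).

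**Assumptions.** Two-sided test, equal split between classes A and B, and the size and shape of the session effect.

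**1. Can control be separated from session 1?** Take one phase of 30 with a fixed effect per person, two free session terms (session 2, session 3) and two treatment terms (placebo, LLLT).
- Parameters: 30 + 2 + 2 = 34. The rank of the design matrix is 33.
- One rank is lost because the indicator of being in session 2 or 3 equals the indicator of receiving placebo or LLLT.
- LLLT–control and placebo–control are not estimable.
- LLLT–placebo is estimable, with variance 2/30 = 0.0667 σ².

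**2. What does assuming a shape buy?** Replace the two session terms by one linear term.
- Parameters: 33. Rank: 33. LLLT–control becomes estimable.
- LLLT falls on average at session (2 + 3)/2 = 2.5, which is 1.5 sessions after control. The estimate is the raw difference minus 1.5 times the slope, and the slope comes from session 3 minus session 2.
- Variance: 2/30 + 1.5² × 2/30 = 0.0667 + 0.15 = 0.217 σ². This is 0.217/0.0667 ≈ 3.25 times that of LLLT–placebo.
- The estimate is valid only if the change from session 1 to 2 equals that from session 2 to 3. A first-session jump breaks this, and the data cannot test it.

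**3. How large could the error be?** Paired t-test of LLLT against control, no laser effect, no session adjustment. Let d be the shift in SDs of the within-person difference. The rejection rate comes from the noncentral t with n − 1 degrees of freedom. The noncentrality is d√n for a one-off shift after session 1, and 1.5d√n for a linear drift of d per session.

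| d (assumed) | One-off, n = 30 | Linear drift, n = 30 | One-off, n = 60 |
|---|---|---|---|
| 0 | 5% | 5% | 5% |
| 0.1 | 8.3% | 12.5% | 11.9% |
| 0.2 | 18.5% | 35.5% | 33.2% |
| 0.3 | 35.5% | 66.4% | 62.8% |

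The last column shows that pooling both phases makes the false result more likely, because the bias stays while the standard error shrinks.

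**4. Which outcomes are exposed?** Lactate (2.6.5), pain (2.6.4) and thermography (2.6.2) each have a baseline in the same session. If change from baseline is analysed, a plain shift in level between sessions cancels, and only a change in the response to the fatigue task would bias the comparison. Torque and EMG (2.6.3, 2.9) are recorded during the contractions and have no such baseline.

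**The case against.** The strongest defence is that the comparison that matters is sound. LLLT versus placebo is randomised in order, hidden from the participant and balanced over sessions 2 and 3, and the article is open about control coming first. This stands. A reader might infer that the trial cannot show an effect of LLLT at all; the documents do not support that.

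Second, no causal claim against control is written down, and the choice of deciding contrast may sit in a fuller plan that is not shown. This stands in part. However, control is listed as a group, the between-group comparisons do not except it, and no analysis plan could recover the contrast without an assumption about the session effect.

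Third, several stronger readings go too far:
- That no model can separate control from session 1. This is true only with unrestricted session effects; step 2 shows that a linear term suffices if it is believed.
- That the error rates are 12%, 36% and 66%. Those belong to linear drift, the very case in which a linear session term would help. A one-off shift gives 8%, 19% and 36%.
- That a useless laser would look effective. Drift in the other direction could equally hide a real effect.
- That the analyst is unblinded. Section 2.5 says that the treatment is hidden from the researcher who analyses the data. Whether that person sees session order is not stated.

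Finally, control-first has merits: everyone meets the task before the randomised sessions, and control cannot be contaminated by laser carry-over. It is a trade-off rather than a plain mistake.

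**Conclusion.** The point holds for comparisons with control, and only for those. LLLT–control and placebo–control are confounded with any first-session effect by design, and this needs no assumed number. Their practical error does rest on assumptions, because the article gives neither size, shape nor direction of a session effect: about 8% to 36% false positives at n = 30 for a one-off shift of 0.1 to 0.3 SD, or 12% to 66% for linear drift of the same size per session, against a nominal 5%. Torque and EMG are most exposed.

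LLLT versus placebo is unaffected. What is wrong as written is that the description of the whole study as randomised and double-blind, and the unrestricted comparison between groups, extend to control a status that only LLLT versus placebo has.

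**What to change.** In sections 2.3, 2.5, 2.8 and 2.10:
- label session 1 a familiarisation or reference session;
- rest the efficacy conclusion on LLLT versus placebo, analysed with a period term for session 2 versus 3;
- report contrasts with session 1 as descriptive.

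In section 2.2 and wherever the terms recur, limit randomised and double-blind to LLLT versus placebo.

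This needs no extra visits or participants and leaves the precision of LLLT versus placebo unchanged. The cost is that the trial gives up a causal claim against no treatment.

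If that claim is wanted and recruitment has not begun, all three conditions could be randomised over six sequences, 30/6 = 5 people per sequence in each phase. The design then has full rank (34 of 34), and each of the three contrasts has variance 0.0667 σ². The price is loss of the common familiarisation session and possible carry-over from LLLT into control in three of the six sequences. Control would remain open to the participant.
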